### Participants

The intervention group participants will be recruited consecutively until we have reached the target of 600 patients. As soon as the patients have signed the consent form, the intervention will start and the baseline data collection will begin. The follow-up period will be one year from the initial assessment for each patient.Inclusion criteria: Patients with emergency admission to the UNN internal medicine department in Tromsø and Harstad who are over the age of 65 years, have two or more long-term conditions and provide valid written informed consent (either by the patient or the next of kin).Exclusion criteria: Language barriers, life expectancy of less than three months and unable to provide written informed consent.

The control population will be recruited from the Nordland Hospital in Bodø and from the hospital UNN Narvik. When an index patient is identified in the hospitals using patient-centred teams, at least two eligible patients from the control hospitals will be identified. Sex, age and number of long-term conditions will be used to match the control patients to the index patients. The control patients will be subject to the same data collection as the intervention patients.

### Sample size

The sample size calculation is based on the primary outcome measure: the Short Form Health Survey (SF-36). The SF-36 has a range from 0 to 100, where 100 is the best possible score, and a standard deviation (SD) of approximately 25 in other populations. Points of two have been shown to be clinically significant [31]. Two different geriatric integrated care interventions similar to ours found differences of 4–6 points between intervention and control groups [32, 33]. We wish to be able to detect a difference of four points in the SF-36 physical health dimension between the intervention and control groups. With 600 patients in each group and a statistical significance level of 0.05, we will have a power of 0.80 to detect such a difference between the groups. We expect this to be realistic based on the existing hospital admission rates. The intervention and control hospitals had approximately 9500 medical emergency admissions for patients aged 67 years and older in 2014 [2].

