### Design

This evaluation study is a prospective non-randomized, matched control, before-and-after study [28]. We will compare all hospitalised patients meeting the inclusion criteria with patients receiving usual care in a control setting. The PACT model is directed at the organisational level or geographic site, affecting all patients within the uptake area. Therefore, the intervention and controls are separated in different hospitals to avoid contamination. The chosen design improves comparability between the patient populations by matching them on factors known to be important for outcomes (age, sex and number of conditions), adjusting for baseline differences between the populations with a before-after design and adjusting for known confounders by the propensity score method [29, 30].

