#### Analyses

The analyses will use an intention-to-treat approach that includes all participants who signed the informed consent at the intervention and control hospitals. Missing data will be imputed using multiple imputations [48]. The multiple imputation model will include predictors from all time points, including health-related quality of life (SF-36), background variables, trial-related variables and resource use at baseline. Results with and without imputed data will be reported. The data will be analysed as a synthetic randomised controlled trial (RCT), using the propensity score method. This method postulates that each patient has a basic probability of the outcome of interest based on his/her characteristics [29]. Based on available knowledge for each patient (e.g. age, sex, education, ethnicity), we can calculate the patient’s propensity for the outcome (i.e. change in QoL). In subsequent analyses, we stratify analyses by this score. Within each stratum, the only known difference between patients with respect to the outcome will be the patient-centred teams. The fundamental requirement for validity in a causal analysis is that the variables used to create the propensity score are independent of the probability of getting the intervention. In common-sense terms, this means that in the synthetic study, within the same propensity score strata, the assignment to treatment is essentially the same as if it had been done by randomisation.

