### Cost-effectiveness evaluation

#### Trial-based economic evaluation

The trial-based economic evaluation consists of a cost-utility analysis with a time horizon of 12 months. The analysis takes a health provider perspective and collects data on health resource use and health outcomes measured in quality-adjusted life-years (QALYs). The economic evaluation will be conducted in accordance with the CHEERS statement [49].

For the economic evaluation, health outcomes will be measured using the SF-6D instrument [50]. The SF-6D will be extracted from the SF-36 and will include physical functioning, role participation (combined role-physical and role-emotional), social functioning, bodily pain, mental health and vitality. The algorithm by Brazier et al. will be used to transform the scores into utility values [51]. The SF-6D scores will be transformed to QALYs by weighing the per-period estimates of utility scores with the time spent in the particular health state, assuming a linear change in utility over time. Imbalances in baseline values will be adjusted for using multiple regression [52].

Only health care costs assumed to be affected by the PACT model and of potential economic significance will be included in the main analysis. Costs borne by patients and productivity losses to society are considered less relevant for the patient group in this study. Two main cost components will be included: the costs related to the PACT model (technology and personnel costs) and the cost related to health services use over the course of the trial (hospital inpatient, outpatient, day hospital and emergency services, community-based health care services and medication). Cost weights will be applied to calculate the costs associated with each primary and secondary health resource activity. These will be collected from hospital accounting databases, national tariffs and official wage and price lists.

The cost-utility analysis will be based on the net-monetary benefit framework (NMB). The NMB approach allows for modelling the variability in the cost effectiveness between the centres and GPs [53]. NMB regression will be used to analyse whether the PACT model is more cost effective for a specific subgroup of patients (the effect modification in RQ 5).

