Dedicated, interdisciplinary patient-centred teams can be a new, more effective and cost-effective way to provide health care to older patients with long-term complex needs. Recent studies and reviews underpin the importance of strategies that support patient involvement, engagement and self-care [57–59]. The active two-way patient–provider dialogues and practical skill development in self-management are reported to be important for better outcomes [60]. The patient-centred teams will ensure that several elements of self-management, such as goal setting, self-monitoring and care plans, will be realised, thereby providing more insights into the relevance of self-management in terms of outcomes and cost effectiveness. In the United Kingdom, the transformation from conventional to patient-centred care in the health system has been estimated to have a cost-cutting potential of 7 % [61].

The strengths of the present study are its real world setting and the involvement of designated health professionals in designing and developing the integrated care model. The PACT model has been initiated and is solely driven by managers and clinical personnel at the hospital and the community services. The structure and organisation of the team and how they work will be continuously adapted to the clinical and everyday routines at the hospitals and in the home care settings. This might increase the probability of sustaining the PACT model after the project has ended.

The main limitation of the study is the lack of randomisation. Although we recognise that randomisation is the most robust method of avoiding systematic bias between comparison groups, this method is not possible in this trial. The PACT model aims to improve geriatric care in terms of both structures and routines at the organisational level of two hospitals. A patient-level randomisation, which requires the organisation to switch between old “usual care” and a new team-based proactive care, is unlikely to be successful [56]. Randomising the organisations could be an alternative, but with only four hospitals, this is too small to make cluster randomisation meaningful. We are therefore using a matched control group with before-and-after comparisons. This design is approved by Cochrane for use in systematic reviews of interventions “*that cannot be randomized, or which are extremely unlikely to be studied in randomized trials*” [28].

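### The stated power of 0.80 assumes no between-hospital variance in the adjusted change, and the claim of as-if-random allocation within propensity strata overlooks that hospital differs in every stratum

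*Protocol article*

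**What the plan says.** - **Power (Protocol article, Sample size).** The target is four points: "We wish to be able to detect a difference of four points in the SF-36 physical health dimension between the intervention and control groups". The SD is taken as about 25. "With 600 patients in each group and a statistical significance level of 0.05", the article says, "we will have a power of 0.80 to detect such a difference between the groups". No ICC, design effect or number of hospitals enters.
- **Level of assignment (Design; Participants).** The model acts on the organisation or geographic site, and "the intervention and controls are separated in different hospitals to avoid contamination". Tromsø and Harstad have PACT; Bodø and UNN Narvik supply the controls.
- **Effectiveness analysis (Analyses).** Patients are analysed as a synthetic RCT with propensity-score strata. "Within each stratum, the only known difference between patients with respect to the outcome will be the patient-centred teams". The subsection adds that allocation inside a stratum can be regarded as though patients had been randomised.
- **Outcome (Outcome measures).** The primary outcome is the adjusted between-group difference in change in the SF-36 physical dimension.
- **Where hospitals are recognised.** The Discussion rejects randomising organisations because "with only four hospitals, this is too small to make cluster randomisation meaningful". In the economic evaluation, "The NMB approach allows for modelling the variability in the cost effectiveness between the centres and GPs", and hospital-specific estimates are promised there.

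**The concern.** Group and hospital coincide completely. Any hospital-specific difference in how patients change over 12 months, and any unmeasured case-mix, is therefore part of the estimated PACT effect. The power statement leaves this variation out, and the within-stratum claims say in effect that it is absent. The Discussion expects the results to guide decisions on funding and expanding PACT. Readers would then take 0.80 and as-if-random allocation as properties of the design, when the first is conditional and the second does not follow.

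**Working it through.** **Inputs from the article.** Difference 4, SD 25, 600 per group, "a statistical significance level of 0.05" (Sample size); two hospitals per group (Participants). Sidedness is not stated. Two-sided is used because it reproduces the stated power, whereas one-sided gives 0.870.

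**Assumptions.** Equal split, 600/2 = 300 patients per hospital. ICC of the adjusted change between 0.001 and 0.01, since the article gives none. Normal reference distribution.

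**Step 1: the plan's figure.** SE = 25 × √(2/600) = 1.443. 4/1.443 = 2.771. Power = Φ(2.771 − 1.96) = Φ(0.811) = 0.791. Exactly 0.80 would need 614 per group. The stated 0.80 is thus reproduced, with a design effect of 1.

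**Step 2: allow for hospital variance.**
- Design effect DE = 1 + 299 × ICC; effective n per group = 600/DE
- Power = Φ(2.771/√DE − 1.96)
- Type I error of a test that ignores hospital variance = 2[1 − Φ(1.96/√DE)]
- 95% half-width = 1.96 × 1.443 × √DE = 2.83 × √DE
- Implied hospital SD = 25 × √ICC

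Example, ICC 0.005: DE = 2.495; n = 600/2.495 = 240; 2.771/√2.495 = 1.754; power = Φ(−0.206) = 0.42; type I error = 2[1 − Φ(1.241)] = 0.21.

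**Step 3: credit for baseline adjustment.** The plan uses the SD of a single score, but the outcome is the adjusted change. With an assumed baseline–follow-up correlation of 0.6, the residual SD is 25 × √(1 − 0.36) = 20. Then 4/(20 × √(2/600)) = 3.464 replaces 2.771.

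| ICC of change | Hospital SD (points) | DE | Effective n per group | Power, SD 25 | Power, SD 20 | Type I error if ignored | Half-width, SD 25 |
|---|---|---|---|---|---|---|---|
| 0 | 0 | 1.00 | 600 | 0.79 | 0.93 | 0.05 | 2.83 |
| 0.001 | 0.8 | 1.30 | 462 | 0.68 | 0.86 | 0.09 | 3.22 |
| 0.002 | 1.1 | 1.60 | 375 | 0.59 | 0.78 | 0.12 | 3.58 |
| 0.005 | 1.8 | 2.50 | 240 | 0.42 | 0.59 | 0.21 | 4.47 |
| 0.01 | 2.5 | 3.99 | 150 | 0.28 | 0.41 | 0.33 | 5.65 |

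Hospital SDs are for SD 25.

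**Step 4: would more patients help?** With two hospitals per group and unlimited patients, the SE tends to √(2 × 625 × ICC/2) = 25 × √ICC. At SD 25, power then tends to Φ(4/1.768 − 1.96) = 0.62 at ICC 0.005 and Φ(4/2.5 − 1.96) = 0.36 at ICC 0.01. At these values recruitment alone cannot restore 0.80.

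**Step 5: the within-stratum claims.** In any stratum, treated patients come only from Tromsø or Harstad and controls only from Bodø or Narvik. The score is built from patient characteristics; the article's examples are age, sex, education and ethnicity. Balancing hospital would require a hospital that supplies both groups, and the design rules that out. Hospital is therefore a second known difference in every stratum, and nothing in the article shows that it has no bearing on change.

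**The case against.** Several counter-arguments have force.

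- **The design already removes much of the difference.** Patients are matched on sex, age and number of conditions, measured confounders are adjusted for, and stable hospital differences in level cancel in the change. This stands, and it narrows the problem to hospital differences in 12-month change and unmeasured case-mix. The ICC that matters is that of the adjusted change, which may be small.
- **Adjustment also reduces patient-level variance.** This stands in part. With residual SD 20, power is still 0.78 at ICC 0.002, but 0.59 at 0.005.
- **Treat the four hospitals as fixed.** Then the patient-level SE is appropriate and 0.79 applies. However, the contrast being tested is PACT together with whatever else separates these hospitals, and the article does not say that its inference is limited in this way.
- **The limitation is acknowledged.** The Discussion names lack of randomisation and the small number of hospitals, and the economic evaluation promises hospital-specific estimates. Neither is carried into the power statement or the primary outcome.

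Two stronger readings are tempting but unsupported. A reader might infer that the planned confidence intervals are too narrow. The Analyses subsection names no variance estimator and does not exclude a hospital term, and an analysis plan that is not shown may settle both. A reader might also quote a hospital-level t-test on 2 df, with power of 0.25, 0.18 and 0.14 at ICC 0.002, 0.005 and 0.01, as the cost of clustering. That test has power of only 0.35 at ICC 0, so most of the fall from 0.79 comes from the 2 df.

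**Conclusion.** The point holds for two statements that the article makes. The power of 0.80 (0.791 recomputed) is right only if there is no between-hospital variance in the adjusted change or, equivalently, conditional on these four hospitals. The claims that the team is the only known difference within a stratum, and that allocation there is as good as random, do not follow from a design with no hospital in both groups.

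The direction is certain for any positive ICC. The size is not, because every ICC used here is assumed. Over 0.001 to 0.01, power runs from about 0.68 down to 0.28 at SD 25, or from 0.86 down to 0.41 at an assumed residual SD of 20, so only a very small ICC is offset. The type I error of about 0.09 to 0.33 applies to a test that ignores hospital variance and is read as inference beyond these four hospitals. It does not describe an analysis that the article has fully specified.

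**What to change.** 1. In Sample size, state that power is 0.79 for four points only if there is no between-hospital variance in change (equivalently, conditional on these four hospitals), and show power over a stated ICC range for the adjusted change.
2. In Analyses, delete or correct the two within-stratum claims. Say that strata balance measured patient characteristics and cannot balance hospital.
3. Report the adjusted SF-36 primary outcome for each of the four hospitals and for each intervention-versus-control hospital contrast. This extends the hospital-specific reporting already planned in the economic evaluation.
4. Add a sensitivity interval for the primary outcome that includes hospital variance over the same ICC range.
5. State that the main p-value is conditional on these four hospitals and does not separate PACT from other hospital differences.

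The cost is a less favourable power statement, a weaker conclusion and a little extra analysis. No more patients are needed.

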### Setting

Trials are often performed on selected patients without comorbidities, causing studies to suffer from limited external validity [34]. Van Royen et al. (2014) argue that there is a driving demand for real-word clinical practice data [35]. In this project, the team members will develop the PACT working routines as part of the daily activities at the hospitals. The model will include medical patients over 65 from an everyday clinical setting, making the trial context naturalistic. The real-world setting and normal patient caseload make the design resemble usual care, thus increasing the generalisability from the trial to other patients in regular practice.

### Outcome measures

The outcomes measures need to match the desired effects of the intervention: the triple aim of improved health and function, improved patient experience and lower costs. The primary outcome is the adjusted differences in the change in the physical health dimension of the Short Form-36 (SF-36) between the intervention and the control groups.

The secondary outcomes are the other dimensions of the SF-36 instrument, health resource use (to measure the costs both in primary and secondary care) and the patient-generated index (PGI) [36]. The PGI registers the patient’s own health complaints at baseline and the severity of these at baseline and follow-up points (the PGI-open format) [37]. The Patient Activation Measure [38] will also be used to measure health self-efficacy. We will use the Patient Assessment of Chronic Illness Care Questionnaire (PACIC) adapted for the Norwegian context [39] to measure how well the patients think the service has been able to support pro-active patient centred care.

Other variables that will be collected are self-reported background information on life-style, socio-economic status and previous health care experiences.

### Data collection and management

Each hospital will have a part-time study nurse based in the geriatric department. The study nurses will administer the consent forms and support the data collection from the patients. The background variables and all the questionnaires will be completed by the patients at baseline, 6 and 12 months.

All data on health service use, including medication, will be collected from electronic information systems. Data on hospital use (hospital admission, length of stay, outpatient consultation, emergencies and medication) will be collected from the hospital records. Data on primary health resource use will be collected from the GPs, the municipalities and other available information systems. Data from the municipalities will supplemented by interviews with the providers. The cost associated with the PACT model itself will be determined by interviewing the PACT members (staff) and reviewing budgets.

### Effectiveness evaluation

#### Health and functional status

To measure health and functional status, the SF-36 was chosen. This is an instrument which researchers across the world have used to describe health-related quality of life in over 4000 publications [40]. Its validity and reliability are high and well documented [41]. The questionnaire has eight domains: physical function, role-physical, bodily pain, general health, vitality, social functioning, role-emotional and mental health. Since the patients in this study will be recruited in a somatic-care setting, the physical function sub-domain has been chosen as the primary outcome measure. The other domains are secondary outcomes.

The scores of the SF-36 do not follow a normal distribution, yet the accepted convention among authors is to use means, standard deviations and ANOVA in statistical analyses. This is possible and desirable because of the high robustness of these statistical methods in the face of non-normal distributions, and because they allow comparison of results with previously published results [42].

#### Patient experiences

The CMM-theory assumes that patients who experience a person-centred approach are more likely to have their personal goals addressed. Furthermore, the CMM assumes that person centeredness improves self-efficacy for health issues and that the patients experience care and service provision that is more sensitive to their needs. The instruments we will use to assess patient experiences are listed below.

The PGI [36] will be used to measure the patients’ personal goal attainment. The PGI registers patients’ own health complaints and their severity at baseline and follow-up [37].

The Patient Health Activation (PAM) instrument will be used to measure self-efficacy. The concept of an informed active patient presumes that if we support a person in their management of their own condition, this will translate into better health and functioning. However, self-management is contingent on motivation, knowledge and skills [38].

The PACIC will be used to assess if the PACT model is in accordance with the pillars of the CCM. The PACIC is developed to measure the presence of patient engagement in self-management, patient involvement in the development of a care plan and the degree of individualised goal setting. The instrument also measures the presence of identifying and solving barriers during care plan implementation as well as the degree of progress of and revisions to the care plan [39]. The PACIC has been validated, shows good reliability and has been widely used. However, correlations between high PACIC scores and care outcomes vary [43–46]. Recent publications indicate that CCM-care is especially important among disadvantaged patients, such as minority groups and patients with a low health activation [44, 47]. In the absence of any other instrument for the purpose of measuring fidelity to CCM-care, we will use the PACIC questionnaire to determine experienced fidelity to the CCM and to explore the interaction with the results collected by the PAM instrument.

